**Methods:**

Patients with acute LBP will be recruited from clinics of general practitioners (GPs) in New Zealand (NZ) and Switzerland (CH). They will be assessed by postal survey at baseline and at 3, 6, 12 weeks and 6 months follow-up. Primary outcome will be disability as measured by the Oswestry Disability Index (ODI); key secondary endpoints will be general health as measured by the acute SF-12 and pain as measured on the Visual Analogue Scale (VAS). A subgroup analysis of different assessment instruments and baseline characteristics will be performed using multiple linear regression models.

This study aims to examine

1. Which biomedical, psychological, social, and occupational outcome assessment tools are identifiers for the transition from acute to chronic LBP and at which time point this transition becomes manifest

2. Which psychosocial and occupational baseline characteristics like work status and period of work absenteeism influence the course from acute to chronic LBP

3. Differences in outcome assessment tools and baseline characteristics of patients in NZ compared with CH.

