**Discussion:**

This study will develop a screening tool for patients with acute LBP to be used in GP clinics to access the risk of developing chronic LBP. In addition, biomedical, psychological, social, and occupational patient characteristics which influence the course from acute to chronic LBP will be identified. Furthermore, an appropriate time point for follow-ups will be given to detect this transition. The generalizability of our findings will be enhanced by the international perspective of this study.

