### Statistical analysis

#### Multivariate identification of predictors for chronicity

Changes in primary and secondary endpoints between baseline data and different time points of follow-up will be analysed by multiple linear regression models. Patients with chronic LBP at 6 months follow-up will be compared with patients without chronic LBP at the same time point.

Patients with chronic LBP in this study are defined as patients with an ODI score without improvement by a Minimal Clinically Important Difference (MCID) of 10 ODI points between T0 (attending the GP for the first time or after a pain free period of at least 6 months) and T4 (6 months follow-up) [84-87].

An analysis of different assessment instruments and baseline characteristics will be performed to find appropriate scores or patient characteristics to identify patients at risk to develop chronic LBP. Different patient assessment tools will be allocated to the following four groups: demographic-biomedical, psychological, social, and occupational risk group [88]. We aim to detect at least one assessment instrument in each group which identifies patients at risk.

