### Sample size/power calculation

#### Sample size considerations

Sample size considerations in clinical studies start from what is considered a MCID. In studies of chronic LBP, the ODI is commonly used as the main outcome measure, and a difference in 10 ODI points is considered clinically relevant. We will consider the sample size and power according to the MCID of ODI.

A minimum of 10 patients with chronic LBP are needed to produce stable estimates for each predicting variable. We will collect data on e.g. 20 potential predictive factors and screen these by logistic regression. If assuming we select four of these predictors for regression modelling, looking for an independent effect, then at least 40 patients with chronic LBP will be needed, 10 patients for each predictor.

We considered a series of scenarios for sample size calculations which resulted in an array of sample sizes between 200 and 800 patients necessary to ensure 80% power at a two-sided p of 0.05. If 5% of patients with acute LBP develop chronic LBP, 800 patients will have to be analysed. However, if 10% or 20% develop chronic LBP at 6 months follow-up only 400 and 200 patients respectively will be needed. Trends from our pilot study including 20 patients in Otago district, NZ show that an even smaller sample size might be sufficient – due to a rate of chronic patients of up to 30% in the pilot sample.

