## Discussion

### Scientific significance

LBP is by far the most prevalent and most costly musculoskeletal problem in our society today [6,10,89,90]. Despite numerous previous studies, to our knowledge there has not been an attempt to comprehensively assess all potential factors which lead to the transition from acute to chronic LBP and the point in the disease progression when this occurs [7].

This study will assess a core set of outcome assessment tools for patients with acute LBP in a GP setting to assess which factors predict whether these patients are at risk of developing chronic LBP [91,92]. In addition, biomedical, psychological, social, and occupational baseline characteristics will be identified which may be found to influence the course from acute to chronic LBP. Furthermore, an appropriate time for follow-ups will be given to increase the likelihood of detecting this transition.

The international perspective of this study of patients in NZ and CH will be an asset in terms of generalizability and validation of our findings for use by others.

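### The article promises a tool that identifies individual patients at risk, but the methods it fixes measure association only, so an instrument with an AUC of about 0.6 could count as an identifier

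*Protocol article*

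**What the plan says.** The product is named in the Discussion part of the Abstract: "This study will develop a screening tool for patients with acute LBP to be used in GP clinics". The Background asks which assessment tools best pick out patients who will become chronic. The statistics section on predictors for chronicity gives the target, across four risk groups (demographic-biomedical, psychological, social, occupational): "We aim to detect at least one assessment instrument in each group which identifies patients at risk".

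The methods are stated in three places:
- Abstract, Methods: "A subgroup analysis of different assessment instruments and baseline characteristics will be performed using multiple linear regression models".
- First subsection of the statistics section: "Changes in primary and secondary endpoints between baseline data and different time points of follow-up will be analysed by multiple linear regression models". After that, those with and without chronic LBP at 6 months are compared.
- Sample size considerations: "We will collect data on e.g. 20 potential predictive factors and screen these by logistic regression". About four factors are then modelled together to look for effects independent of one another.

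The sample size follows from that model: "then at least 40 patients with chronic LBP will be needed, 10 patients for each predictor". The only error rate and power in the article describe the resulting sample sizes: "necessary to ensure 80% power at a two-sided p of 0.05".

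Under Scientific significance, the two-country perspective is credited in these words: "will be an asset in terms of generalizability and validation of our findings for use by others".

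**The concern.** A regression coefficient or a group comparison answers whether chronic and recovering patients differ on average. A screening tool must answer whether an individual's score separates the two groups well enough to act on. A small mean difference can be firmly established while the two score distributions overlap almost completely. The larger the sample, the smaller the difference that can be established.

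The target is phrased in the language of classification, but every method attached to it is a method for association. If the analysis is carried out as described, the study can report an instrument in each risk group that identifies patients at risk when none would be useful in a GP clinic. The Background's question of which tools identify best would stay open, because the stated analyses do not rank instruments by how well they separate patients.

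**Working it through.** **The plan's own figure.** Ten chronic patients per predictor times four predictors gives 40. Dividing by the assumed chronicity rates gives 40/0.05 = 800, 40/0.10 = 400 and 40/0.20 = 200, exactly as stated. The accompanying claim of 80% power cannot be reproduced: no effect size is given, and a rule of 10 events per predictor does not involve power.

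**What an association criterion lets through.** The inputs from Sample size considerations are 40 chronic patients, totals of 800, 400 and 200, two-sided 0.05, and 80% power. My assumptions are:
- scores are normal with equal variance in both groups;
- 0.05 is the level at which an association would be called;
- specificity takes a range of values, because the article gives none.

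With e chronic patients among N, and differences in SD units:
- just significant: d = 1.96 × √(1/e + 1/(N−e))
- detected with 80% power: d = (1.96 + 0.84) × √(1/e + 1/(N−e))
- AUC = Φ(d/√2)
- proportion missed at specificity Sp = 1 − Φ(d − z(Sp))
- balanced cut-off: sensitivity = specificity = Φ(d/2)

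Example with N = 400 and e = 40: √(1/40 + 1/360) = 0.167, so d = 0.327 (just significant) or 0.467 (80% power). For the latter, AUC = Φ(0.330) = 0.629. Sensitivity at 90% specificity is Φ(0.467 − 1.282) = 0.208, so 79.2% are missed.

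| N, chronic rate | d, AUC just significant | d, AUC at 80% power | missed at 90% specificity* | missed at 80% specificity* | missed at balanced cut-off* |
|---|---|---|---|---|---|
| 800, 5% | 0.318, 0.589 | 0.454, 0.626 | 79.6% | 65.1% | 41.0% |
| 400, 10% | 0.327, 0.591 | 0.467, 0.629 | 79.2% | 64.6% | 40.8% |
| 200, 20% | 0.346, 0.597 | 0.495, 0.637 | 78.4% | 63.5% | 40.2% |

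*For the 80%-power instrument. Over specificities from 50% to 95%, its miss rate in these scenarios runs from 31% to 88%.

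Predictive value, N = 400 at 90% specificity: 0.208 × 0.10 / (0.208 × 0.10 + 0.10 × 0.90) = 0.19, against a base rate of 0.10.

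**Larger sample.** Data collection expects 792 analysed patients. At 10% chronic (79 patients), a just-significant instrument has d = 0.232 and AUC 0.57. At the pilot's 30%, it has d = 0.152 and AUC 0.54. More data admit weaker instruments.

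**Several instruments together.** Four independent instruments of d = 0.467 combine to d = 0.467 × √4 = 0.934. AUC = Φ(0.660) = 0.75, and the proportion missed at 90% specificity is 1 − Φ(0.934 − 1.282) = 64%. Correlated instruments would add less.

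**Benchmarks.** Sensitivity and specificity of 70% each need d = 1.05 (AUC 0.77). Catching 80% at 90% specificity needs d = 0.84 + 1.28 = 2.12 (AUC 0.93).

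**The case against.** The strongest reply is that this is a condensed article. Performance measures, cut-offs and calibration are commonly left to a full protocol or analysis plan, which is not shown. Logistic regression is also a sound basis for a screening tool, since it yields predicted risks from which discrimination can be calculated, and nothing stated rules that out. This stands so far as it goes: the absence of an AUC from the article is not an error in itself, and the choice of logistic regression is not at fault. The point rests on what the article does fix, namely a classification target tied to methods that are all about association.

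Three stronger readings are tempting and are not supported:
- **That instruments qualify by p below 0.05.** The article states no such rule. The 0.05 level belongs to the sample-size scenarios and is not attached to the logistic screening or to the choice of predictors. Its use above is an assumption.
- **That the promised tool would miss 80% of chronic patients.** That figure is for one instrument of a particular strength at an assumed 90% specificity. It is one point on a wide range, and a tool combining several instruments would do better.
- **That the study will declare its tool validated.** The remark under Scientific significance is a general Discussion statement about the value of two countries. It does not announce a validation result. The only country analysis stated looks for differences between NZ and CH.

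**Conclusion.** The concern holds in a limited form. The promised product and the target require classification of individuals, the named methods deliver associations, and the article does not define what it means to identify a patient at risk. In the plan's own scenarios, an instrument at the edge of detectability has an AUC of 0.59 to 0.64, and with 792 patients it could be as low as 0.54. That is weak discrimination whichever cut-off is chosen, so this conclusion does not depend on the assumed specificity, although each quoted miss rate does. All figures rest on normal scores with equal variance and on 0.05 as the working level. They show what could pass, not what the study will find: an instrument may turn out far stronger than the minimum.

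**What to change.** In the statistics section on predictors for chronicity:
1. State beforehand what performance counts as identifying patients at risk. The threshold is for the sponsor to choose and justify, but it must be well above an AUC of 0.5, since a floor there would largely restore the association criterion.
2. Rank each instrument, and judge the final logistic model, by discrimination: AUC with 95% CI, and sensitivity, specificity and predictive values at a cut-off fixed in advance. Report calibration of the model.
3. Correct the selected model's performance for optimism, for example by bootstrap with the selection step repeated in each sample. About 20 factors screened on 40 chronic patients is 40/20 = 2 per candidate, so apparent performance will flatter the tool.
4. As a secondary check, apply the model across NZ and CH only where each country has enough chronic patients for the plan's own rule of 10 per predictor. With 20 per country and four predictors there would be 20/4 = 5, half of what the rule asks. Where the rule is not met, do not describe the result as validated.

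The cost is wording and further analysis of data already planned, with no extra patients for items 1 to 3. Fewer instruments may qualify. Country-level AUCs would be imprecise: at an AUC of 0.70 the Hanley-McNeil 95% half-width is about 0.13 with 20 chronic and 180 non-chronic patients, and about 0.09 with 40 and 360.

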#### Identification of time of chronicity

In a second step, a subgroup analysis on patients without chronic LBP will be performed to identify the time of follow-up (TX) where this patient group shows an improvement in ODI by at least the MCID. As patients with chronic LBP by definition of their condition don't show an improvement at TX, this follow-up is the most appropriate time point for detecting the transition from acute to chronic LBP in patients at risk.

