#### Hypotheses

Three hypotheses will be examined:

1. Specific biomedical, psychological, social, and occupational outcome assessment tools are identifiers for the transition from acute to chronic LBP at a time point between 3 and 12 weeks.

2. Specific psychosocial and occupational baseline characteristics like work status and period of work absenteeism influence the course from acute to chronic LBP.

3. There are differences in patient outcome assessment tools and baseline characteristics between patients in NZ and CH, e.g. in disability compensation systems.

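### TX is set only from patients already known to have improved at 6 months, and the claim that chronic patients cannot have improved at TX holds only if TX is the 6-month visit

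*Protocol article*

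**What the plan says.** The protocol article, under Study design, schedules follow-up at 3, 6 and 12 weeks and at 6 months (T1 to T4). Under Multivariate identification of predictors for chronicity, chronic LBP means "patients with an ODI score without improvement by a Minimal Clinically Important Difference (MCID) of 10 ODI points between T0" and T4. The article states there that "Patients with chronic LBP at 6 months follow-up will be compared with patients without chronic LBP at the same time point". The same section plans linear regressions of change from baseline to the different follow-ups.

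Under Identification of time of chronicity, a second step is restricted to the patients without chronic LBP. TX is the follow-up "where this patient group shows an improvement in ODI by at least the MCID". The justification is: "As patients with chronic LBP by definition of their condition don't show an improvement at TX". From this the article concludes that "this follow-up is the most appropriate time point for detecting the transition from acute to chronic LBP in patients at risk".

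Hypothesis 1 says that certain assessment tools are "identifiers for the transition from acute to chronic LBP at a time point between 3 and 12 weeks".

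**The concern.** A visit is useful for detecting the transition if, at that visit, patients who will be chronic at 6 months look different from those who will not. The rule for TX uses one of these two groups only, and that group was formed by its outcome at T4. The other half of the comparison is supplied by an assertion about chronic patients, which the definition supports at T4 and nowhere earlier.

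The timing of the transition is the second half of aim 1 and part of hypothesis 1. A recommended time for follow-up is also promised in the Abstract and the Discussion, as an aid to GPs. If TX reflects only how fast recoverers recover, that recommendation would name a visit whose ability to separate the two groups has not been examined by the rule that chose it.

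**Working it through.** **Inputs from the article.** The threshold is 10 ODI points (Sample size considerations: "a difference in 10 ODI points is considered clinically relevant"). The visits are T1 to T4 at 3, 6 and 12 weeks and 6 months. The expected analysed sample is 792 (Data collection). The article gives no figure for TX to reproduce.

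**Step 1: a TX always exists.** Let D1 to D4 be a patient's ODI improvement from T0 to each visit. Chronic means D4 < 10, so non-chronic means D4 ≥ 10. Every member of the analysed group has D4 ≥ 10. The group mean at T4, the median at T4 and the proportion improved at T4 (100%) therefore all satisfy the rule, however it is summarised. The rule is met at T4 if not before. This needs no assumption.

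**Step 2: the by-definition statement.** The definition restricts D4 only. If TX = T4, chronic patients have not improved at TX, but this merely restates the definition. If TX is T1, T2 or T3, a patient with D ≥ 10 at that visit and D4 < 10 is chronic and had improved at TX. Nothing in the definition excludes this patient. The statement is thus guaranteed only at the one visit that lies outside the 3 to 12 week window of hypothesis 1.

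**Step 3: illustration.** The article gives no SD of ODI change, no course over time and no correlation between visits, so these are assumptions: normal improvements with SD 15, equal correlation r between visits, n = 792, 1,000 replicates, and TX read as the first visit at which the non-chronic mean improvement is at least 10. A TX was returned in every replicate of every scenario.

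| Mean improvement T1/T2/T3/T4 | r | Chronic at T4 | TX | Chronic improved ≥ 10 at TX | Non-chronic improved ≥ 10 at TX |
|---|---|---|---|---|---|
| 15/18/20/22 | 0.8 | 21% | T1 always | 13.7% | 76.2% |
| 15/18/20/22 | 0.5 | 21% | T1 always | 34.8% | 70.6% |
| 15/18/20/22 | 0 | 21% | T1 always | 62.9% | 63.2% |
| 12/18/24/29 | 0.5 | 10% | T1 always | 20.3% | 59.4% |
| 0/0/0/0 | 0.5 | 75% | T1 29%, T2 17%, T3 10%, T4 44% | 9.8% | 72.7% |
| 0/0/0/0 | 0 | 75% | T4 always | 0% | 100% |

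The first three rows have the same mean course and the same TX. Only r differs, and how well TX separates the groups runs from good to nil. The rule cannot tell these cases apart.

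A check by formula for these rows: z = (10 − 22)/15 = −0.8, with normal density φ = 0.290 and distribution function Φ = 0.212.
- Mean improvement of chronic patients at T1: 15 − r × 15 × φ/Φ = 15 − r × 15 × 1.367. This is −1.4, 4.7 and 15.0 for r = 0.8, 0.5 and 0.
- Mean improvement of non-chronic patients at T1: 15 + r × 15 × φ/(1 − Φ) = 15 + r × 15 × 0.368. This is 19.4, 17.8 and 15.0.

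In the fifth row nobody truly improves on average, yet selection on T4 alone lifts the expected non-chronic mean at T1 to T3 to about 9.5 points (0.5 × 15 × φ(0.667)/(1 − Φ(0.667))). Sampling variation then carries it past 10 before T4 in 29% + 17% + 10% = 56% of replicates.

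**The case against.** **A group-level reading.** The sentence may mean that chronic patients as a group do not improve. As an approximation this may be fair. Another simulation assumed baseline ODI 30 (SD 16), 80% of patients recovering by 85% with a 5-week time constant, and a visit-to-visit SD of 5 to 12. The chronic group's mean change at T1 to T3 stayed between about −3 and +2 points, against roughly 13 to 27 in the non-chronic group. So the rule is not shown to be uninformative. What stands against this reading is that such a contrast is a matter for the data, and the article presents it as true by definition.

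**Three stronger readings that a reader might infer.** None is supported.
- *The timing hypothesis cannot fail.* It can. Which visit becomes TX depends on the data, and TX = T4 would fall outside 3 to 12 weeks. Only the existence of some TX is guaranteed. The part of hypothesis 1 about assessment tools is not tested by TX at all.
- *The two groups are never compared before 6 months.* The article describes no such comparison at T1 to T3. But its regressions of change at different follow-ups are not restricted to non-chronic patients, and the article condenses a fuller plan. What can be said is that TX itself is set from the non-chronic group alone.
- *The rule will pick 3 weeks.* That follows from an assumed fast recovery and from reading the rule as a mean change, which the article does not specify. In the simulation just described, a 14-week constant leaves the non-chronic mean at about 6 to 9 points at T1, and TX moves to 6 weeks.

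**The inputs.** The percentages are illustrative. Zero correlation between repeated ODI scores in one patient is implausible, and the no-improvement rows have 75% chronic, far above the 5% to 30% considered under Sample size considerations. The simulation in this objection also gave about 31% to 33% chronic at the 5-week constant, slightly above that range. Steps 1 and 2 need none of these inputs.

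**Scope.** This is a second-step analysis. The ODI endpoint, the predictor analysis, the sample size and the visit schedule are unaffected.

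**Conclusion.** The point holds, and the passage is wrong as written. TX is derived from a group selected on its T4 improvement, so some TX is always returned. The reason given for treating TX as the best detection time is true only when TX = T4. For any earlier visit, patients who improve and then relapse contradict it. The rule describes speed of recovery among recoverers, and the step from there to a detection time does not follow.

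These conclusions rest on the article's own definition and rule and need no numerical assumption. How much it matters in practice depends on the spread of ODI change, its course and its correlation between visits, none of which the article gives. Under the assumed inputs with 10% to 21% chronic and a correlation of 0.5 to 0.8, between 14% and 35% of chronic patients had improved by 10 points at TX. This shows the mechanism and is no estimate for this study.

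**What to change.** Delete the sentence that says chronic patients by definition show no improvement at TX. Replace the subgroup analysis with one on all patients that compares T4-chronic with T4-non-chronic patients at each of T1, T2 and T3, and report:

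- the proportion in each group that has improved by at least 10 ODI points at that visit;
- how well ODI at that visit, with baseline ODI in the model, predicts T4 status, for example sensitivity, specificity and AUC with confidence intervals. Other measures of discrimination would also serve.

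State before analysis the criterion by which TX is chosen, and allow the result that no visit before T4 meets it. Note in the report that change scores at T1 to T3 and at T4 share the T0 measurement, which can by itself create apparent discrimination. This is why ODI at the visit with baseline ODI in the model is preferable to the change score alone.

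The cost is a change of wording and a few extra tables. ODI is already to be collected from all patients at every visit, so no new data, visits or patients are needed.
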